#### Cost-effectiveness analysis

A cost-effectiveness analysis will be carried out by calculating the incremental cost-effectiveness ratio (ICER), which represents a single, common effect that measures the difference in magnitude between the two alternatives using data retrieved from a clinical trial, expressed in terms of the incremental cost per unit of effect, as follows:$$ ICER=\left(Cos{t}_a-Cos{t}_b\right)/\left( Effectivenes{s}_a- Effectivenes{s}_b\right), $$where the measures of effectiveness will be considered to be the satisfaction with the dentures and the OHRQoL impacts.

Decision analysis will be carried out to model the outcomes of decision between the two alternatives. This analysis considers that the outcomes of decisions are not certain, but that the probabilities of different outcomes are known from the trial-based data. The Markov model with Monte Carlo simulation will be used since the decision analysis problem involves risk that is continuous over time, the timing of events is important, and important events may happen more than once.

Markov models assume that a patient is always in one of a finite number of discrete health states, called Markov states [37]. All events are represented as transitions from one state to another. Important events for this study will be represented in a tree-type diagram that identifies the decision alternatives (decision node), the list of the possible outcomes of each alternative (chance nodes) and the sequence of events (terminal node). The full decision tree will contain all the relevant nodes and the paths between them, as well as the probabilities assigned to chance events and the values attached to each potential final state. Data derived from the clinical trial will be used to construct a Markov decision-tree model of CD versus SIMO, considering the most relevant clinical events, their related probabilities of transitions from one state to another) and estimated costs from each course of action.

One-way sensitivity analysis will be performed to assess the impact that changes in certain parameters (e.g., implant/component costs, time horizon, etc.) will have on the model’s conclusions, as well as to determine which parameters are the key drivers of a model’s results. A tornado diagram will be constructed to show graphically the results of various assumptions on the final outcome in the sensitivity analysis. TreeAge Pro 2014 software will be used for the cost-effectiveness analysis.

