**Methods/design:**

This randomized clinical trial will include edentulous individuals who meet eligibility criteria. Participants will be randomized into one of the treatment groups: a conventional complete denture group or a single-implant mandibular overdenture group. Direct costs related to therapies in both groups will be identified, measured and valuated for 1 year after treatment. Oral health-related quality of life and satisfaction with the dentures will be the primary outcome variables. Incremental cost-effectiveness ratios will be estimated and graphically presented on cost-effectiveness planes. A Markov decision tree will be constructed to set out the consequences of the competing alternatives. Sensitivity analysis on the most important assumptions will be performed in order to assess the robustness of the model.

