### Sample size estimation

In this study, sample size was estimated for each of the two treatment groups considering a minimum power of 0.80 (type II error rate) at a two-sided 0.05 significance level (type I error rate). A previous single-group clinical trial that assessed the incremental effect of the SIMO treatment compared to the CD, and considered the outcome satisfaction with the dentures and OHRQoL, served as the data source for this sample size estimation [23]. A minimum of 24 patients will enter this two-treatment parallel-design study, considering that the true difference between treatments is 7.4 units for OHIP-EDENT and 2.6 units for satisfaction scores, assuming unequal variances for both groups. An increase of 10 % to reduce the impact of loss to follow-up on study power resulted in a minimum final sample of 28 participants, 14 in each treatment group.

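### No described step carries the sampling error of a minimum of 14 patients per arm into the ICER or the model of up to 10 years

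*Protocol article*

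**What the plan says.** All references are to the protocol article.

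- **Inputs to the model.** Under Cost-effectiveness analysis, decision analysis is described as recognising that outcomes are uncertain, "but that the probabilities of different outcomes are known from the trial-based data". The source is this trial: "Data derived from the clinical trial will be used to construct a Markov decision-tree model of CD versus SIMO".
- **Simulation.** "The Markov model with Monte Carlo simulation will be used since the decision analysis problem involves risk that is continuous over time". The remaining reasons in that sentence are that event timing matters and that events can recur.
- **Sensitivity analysis.** "One-way sensitivity analysis will be performed to assess the impact that changes in certain parameters". The examples given are implant and component costs and the time horizon, in an open-ended list. The display is also stated: "A tornado diagram will be constructed to show graphically the results of various assumptions on the final outcome in the sensitivity analysis".
- **Display of the ICER.** The abstract (Methods/design) says: "Incremental cost-effectiveness ratios will be estimated and graphically presented on cost-effectiveness planes". What will be plotted on the planes is not stated.
- **Inference.** Under Descriptive and inferential statistics, the planned comparisons cover OHIP and patient satisfaction. Costs and the ICER are not among them.
- **Size and horizon.** Under Sample size estimation: "A minimum of 24 patients will enter this two-treatment parallel-design study", raised by 10% to a minimum of 28, or 14 per arm. Under Time horizon and discount rates, primary data cover one year and the model may run to 10 years.

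**The concern.** Cost-effectiveness is the stated aim of the trial, and the hypothesis in the Background is that the implant's extra cost is small in relation to what it achieves. That is a statement about a ratio of two estimated differences. Each difference comes from about a dozen patients per arm, and the ratio is then extended by a model whose transition probabilities come from the same patients.

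The plan does set out how it will deal with uncertainty: it names the type of sensitivity analysis, its display, the simulation method and the software. What it names does not address sampling error in the model inputs jointly. A one-way analysis moves one input while the others stay fixed, so it cannot show how costs, effects and event probabilities vary together. It also gives no probability that the overdenture is cost-effective at a given willingness to pay. The examples offered are a price and a structural choice, not quantities estimated with error from the trial. A point ICER with a tornado diagram would leave the reader unable to judge the hypothesis.

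**Working it through.** **1. The plan's own figure.** Before dropout there are 24 patients, or 12 per arm at 1:1 allocation. With a 10% allowance, 12/(1 − 0.10) = 13.3 and 12 × 1.10 = 13.2. Both round up to 14 per arm, 28 in total, so the stated minimum reproduces.

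**2. Does any described step carry parameter error forward?**

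| Step described | Does it carry sampling error into the ICER or the model? |
|---|---|
| *t* tests or nonparametric tests | Only for OHIP and satisfaction taken alone; not for costs or the ratio |
| Markov model with Monte Carlo simulation | Not as described: the reasons given are continuous risk, timing and recurrence, and no parameter distributions are mentioned |
| One-way analysis, tornado diagram | One input at a time; not jointly |
| Cost-effectiveness planes | Content not stated; without resamples or parameter draws a plane shows only points |

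Patient-level simulation around fixed probabilities reproduces chance variation between simulated patients. It does not reflect error in the probabilities themselves.

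**3. How imprecise is a probability from 14 patients?** The event counts are assumed for illustration. The intervals are exact (Clopper–Pearson) 95%. For 0/14 the upper limit is 1 − 0.025^(1/14) = 0.232.

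| Events in 14 | One-year estimate | 95% interval |
|---|---|---|
| 0 | 0% | 0 to 23.2% |
| 1 | 7.1% | 0.2 to 33.9% |
| 2 | 14.3% | 1.8 to 42.8% |

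With 12 patients, 0 events gives 0 to 26.5% and 1 event gives 0.2 to 38.5%.

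**4. How imprecise is the denominator of the ICER?** The protocol gives no SD, so one has to be implied. A two-sided 0.05 *t* test with 12 per arm and exactly 80% power needs a standardised difference of 1.197. The implied common SD is 7.4/1.197 = 6.18. (The normal approximation implies 6.47.)

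At 14 per arm, with an observed difference of 7.4:

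- SE = 6.18 × √(2/14) = 2.34
- half-width = 2.056 × 2.34 = 4.80 (26 degrees of freedom)
- 95% interval = 7.4 ± 4.80 = 2.6 to 12.2

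With incremental cost held fixed, the ICER is proportional to 1/difference:

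- lower: 7.4/12.20 = 0.61 times the point value
- upper: 7.4/2.596 = 2.85 times the point value

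The range across assumptions is as follows.

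| Patients per arm | Common SD | 95% interval for the difference | ICER multiple |
|---|---|---|---|
| 14 | 6.18 | 2.6 to 12.2 | 0.61 to 2.85 |
| 14 | 6.47 | 2.4 to 12.4 | 0.60 to 3.12 |
| 12 | 6.18 | 2.2 to 12.6 | 0.59 to 3.42 |

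The second row uses SE = 6.47 × √(2/14) = 2.445 and half-width 2.056 × 2.445 = 5.03.

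Steps 3 and 4 each vary one quantity. They show how imprecise the inputs are. They do not measure the joint uncertainty, which also depends on the spread of costs and on the correlation between cost and effect; the protocol gives neither.

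**The case against.** Several points on the other side have force.

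- **Monte Carlo may mean parameter draws.** The article does not say whether draws are over patients or over parameters. A reader might infer that the plan ignores sampling error altogether, and the text does not support that. It supports only that no described step propagates the error, and that the reasons given lean towards patient-level simulation.
- **The word *known* may be idiom.** It can be read as the usual description of decision-making under risk, naming the trial as the source of inputs, rather than as a denial of sampling error. That is fair, but it changes nothing in the result unless distributions are assigned, and none are described.
- **The list of sensitivity parameters is open.** Transition probabilities are not excluded. Even if they were included, a one-way analysis would not show joint uncertainty.
- **An article condenses.** Resample counts and distribution families belong in a fuller document, and their absence is not the point here. The point is the uncertainty method that the article does state.
- **A reader might infer that the reported uncertainty will be spuriously narrow.** The plan describes no interval for the ICER. The problem is uncertainty left unreported, not an interval that is too tight.
- **Larger headline figures are available.** Compounding the upper limit for 0/14 over ten cycles gives 1 − (1 − 0.2316)^10 = 93%. That needs a constant annual risk, which the protocol does not state, and the longest permitted horizon. The Background also reports high implant success at this site. It is a worst case and should not carry the argument.
- **28 is a minimum.** More patients would narrow the intervals, but the described method would still not carry them into the ICER.

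**Conclusion.** The point holds in a limited form. The plan names only a one-way sensitivity analysis, leaves the type of Monte Carlo simulation unspecified, takes the trial-based probabilities as known, and confines inference to the effectiveness outcomes. As described, the joint sampling error in costs, effects and probabilities does not reach the ICER or the longer-term model. This concerns the trial's central question and should be changed before analysis.

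The size is illustrative. One-year risks would carry intervals such as 0 to 23% or 0.2 to 34%, and uncertainty in OHIP-EDENT alone would spread the ICER over about 0.6 to 2.85 times its point value. These figures assume event counts of 0 or 1, exactly 14 analysed patients per arm, an observed difference equal to the planned one, a common SD implied by the power statement (the protocol assumes unequal variances and gives no SD), and fixed incremental cost.

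**What to change.** 1. **Within-trial ICER.** Bootstrap patient-level cost-effect pairs within each arm (for example 5,000 resamples) and plot the resamples on the cost-effectiveness plane. Report the resulting uncertainty and an acceptability curve over a stated range of willingness to pay. If resamples fall in more than one quadrant, an interval for the ratio is hard to interpret and the acceptability curve should lead. Cost items that Table 2 averages over cases add no between-patient variation, and the report should say so.
2. **Markov model.** State that the Monte Carlo simulation includes parameter draws, for example Beta or Dirichlet for probabilities and Gamma for costs. Specify the prior used when an event count is zero.
3. **One-way analysis.** Keep the tornado diagram as supplementary and include the transition probabilities among its parameters.
4. **Wording.** Describe the probabilities as estimated from the trial rather than known.

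The cost is modest extra analysis time, and the reported uncertainty will be wider and less favourable. No new data or patients are needed.

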## Discussion

This is the first trial-based cost-effectiveness study on SIMOs. Specific challenges in designing the protocol are considered. The expected results are of high clinical relevance and may contribute to the clinical decision-making process, offering a novel approach for the treatment of mandibular edentulism.

The scarcity of economic analysis in prosthodontics has major practical implications, since clinical decision-making might occur without there being reliable evidence relating to the costs and consequences of prosthodontic care. Therefore, the best possible decision cannot always be achieved in the scenario of limited financial resources [38]. Another critical challenge to conduct cost-effectiveness analysis in prosthodontics is to incorporate validated clinical outcomes that can be used to compare and contrast costs of the intervention [38]. This study protocol suggests two commonly used patient-reported measures for edentulous subjects: a validated instrument for assessment of OHRQoL impacts and a multi-item measure of patient satisfaction with the mandibular denture. The definition of resource items, criteria for cost calculation and sources for item valuing are also proposed.

The incorporation of implants as part of oral rehabilitation alternatives also gives rise to important issues regarding health economics. Since many implant interventions involve relevant costs for both the patient and prosthodontist, the search for a more efficient use of available resources to achieve better benefits with lower costs is mandatory in many clinical situations. A systematic literature review [39] on economic aspects of implant interventions, focusing on cost-effectiveness of dental implants compared with other conventional treatment options, showed that replacement of multiple teeth with dental implants was associated with higher initial costs along with greater improvements in patient-reported outcomes. However, there is an evident lack of studies dealing with measurement of costs and consequences in specific clinical scenarios involving edentulous subjects and implants. This is both surprising and disappointing because this type of study is essential due to concern about the increase in health care expenditure associated with limited resources to meet the demands of both patients and society [40].

Finally, from an economic perspective, it is important to bear in mind that, in most societies, dental care is not fully incorporated as an integral part of general health services. Hence, there is a predominance of private dental care based on the fee-for-service payment system, in which dentists are paid for every service that they provide based on the usual and customary fees charged in the local area. This probably explains why there is scarce evidence derived from economic studies in dentistry [41, 42] and reinforces the need for economic evaluations of dental interventions, in order to improve decision-making processes and contribute to the development of health care policies.

## Trial status

The trial started recruitment in March 2016.

## Abbreviations

CD: Conventional denture
ICER: Incremental cost-effectiveness ratio
ISQ: Implant stability quotient
OHIP-EDENT: Oral Health Impact Profile for Edentulous
OHRQoL: Oral health-related quality of life
PPP: Purchasing power parity
SIMO: Single-implant mandibular overdenture
